## Methods/Design

### Objectives, endpoints and sample size calculation

This clinical trial is designed to investigate the hypothesis that watchful waiting is not inferior to surgical repair of asymptomatic and oligosymptomatic incisional hernias in terms of pain and discomfort during normal activities.

To rule out published or ongoing trials dealing with the same subject, a literature search was done. Searching PubMed using the terms "incisional hernia AND watchful waiting" retrieved no matching results. "Incisional hernia AND randomized trial" retrieved 180 hits, but no randomized trial comparing watchful waiting to surgical repair. By searching relevant websites http://www.clinicaltrials.gov, http://www.actr.org.au, http://www.umin.jp/ctr/index.htm, http://www.trialregister.nl, http://isrctn.org, no randomized trial comparing watchful waiting vs. surgical repair in incisional hernia could be identified.

The primary efficacy endpoint is pain/discomfort during normal activities as a result of the hernia or hernia repair 2 years after enrolment, as measured by the hernia-specific Surgical Pain Scales (SPS). Studies show that a long term follow up is needed because postoperative pain may decrease with time [16]. Participants are asked to rate the average pain during the last 24 hours on a 150 mm visual analog scale varying from "no pain sensation" to "most intense pain imaginable". The Surgical Pain Scales were introduced by McCarthy et al. Intraclass correlation coefficients for SPS were 0.95 and 0.94. Correlations varying from 0.44 to 0.60 between the visual analog scales and the bodily pain dimension on the SF-36 and significant differences between SPS levels for patients requiring more and less time to resume normal activities (p = 0.015 to p = 0.002) supported the validity of the scales [17]. SPS scores are measured at baseline and at follow-up visits after 6, 12, 18 and 24 months.

The sample size calculation is based on the non-inferiority of the experimental intervention. A mean SPS score of 12.0 with a SD of 12.0 and 12.0 and an expected mean difference of 0.5 in favor of the surgical intervention group is assumed after a two-year follow-up.

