Participants randomized into the watchful waiting group will receive standardized oral information and written instructions which, like those described by Fitzgibbons et al., will deal with physical activity, diet, pain and pain medication, constipation management, sexual activity, hernia warning signs, and symptoms of acute incarceration [24]. They will be told to consult a physician immediately if acute symptoms develop. Physical examinations will be performed during follow-up visits at 1 month, 12 months and 24 months by a physician. After 6 and 18 months, participants will also be interviewed regarding potential hernia-related pain or discomfort by a physician or a study nurse. The frequency and scope of study visits is presented in table 1.

**Table 1 T1:** Frequency and scope of study visits

Visit	Visit 1 (Screening)	Visit 2 (Day of surgery)	Visit 3 (1 month post OP)	Visit 4 (6 months post OP)	Visit 5 (12 months post OP)	Visit 6 (18 months post OP)	Visit 7 (24 months post OP)
Demographics and baseline clinical data	X						

Inclusion/exclusion criteria	X						

Randomization	X						

Clinical examination	X		X		X		X

Ultrasound	X						X

Pain level (SPS, PDI)	X			X	X	X	X

Quality of life (SF-36)	X			X	X	X	X

Mental health (HADS-D)	X						X

Patient satisfaction (Likert scale)	X			X	X	X	X

Surgical intervention		X					

Postoperative complications			X		X		X

AEs/SAEs		X	X	X	X	X	X

Costs of treatment		X	X	X	X	X	X

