An initiation meeting in Berlin took place in January 9, 2012 to introduce the principal investigators and to familiarize the study centers with the details of screening, randomization, surgery, monitoring and follow-up. The whole study team was present. The first patient was randomized at Charité Campus Benjamin Franklin November 14, 2011.

The recruitment period is planned for 36 months (until October 2014); last-patient-out should be achieved in November 2016.

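### The primary endpoint is timed from enrolment, but Table 1 times the 24-month SPS reading and every other follow-up visit from surgery

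*Protocol article*

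**What the plan says.** In the protocol article, *Objectives, endpoints and sample size calculation*, the primary endpoint is "pain/discomfort during normal activities as a result of the hernia or hernia repair 2 years after enrolment". The same section lists the measurement times without naming their origin: "SPS scores are measured at baseline and at follow-up visits after 6, 12, 18 and 24 months".

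Table 1, in *Implementation of the study*, is the only visit schedule shown. It puts randomisation at Visit 1 (screening), followed by "Visit 2 (Day of surgery". The follow-up columns then run from "Visit 3 (1 month post OP" to "Visit 7 (24 months post OP", and the final SPS is marked in that last column. No interval between Visits 1 and 2 is stated.

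Table 1 is introduced at the end of the paragraph on the watchful-waiting arm, as the schedule of study visits in general. For that arm the paragraph says: "Physical examinations will be performed during follow-up visits at 1 month, 12 months and 24 months by a physician". Interviews are added at 6 and 18 months. Here too no origin is named.

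Under *Trial status*, recruitment is planned until October 2014 and "last-patient-out should be achieved in November 2016".

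**The concern.** The article gives two incompatible times for one reading, and that reading is the primary endpoint. An intention-to-treat comparison needs the same time zero and the same assessment time in both arms. If sites or the eCRF follow the Table 1 labels, the repair arm is read at enrolment plus the wait for surgery plus 24 months. Watchful-waiting patients, who have no operation date, can only be read from enrolment. Time since randomisation then differs systematically by arm.

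This is not harmless by assumption. The article justifies its long follow-up on the ground that "postoperative pain may decrease with time", so it treats the outcome as depending on time since surgery. The planned true difference is only 0.5 on the SPS, so a modest timing effect would be large relative to it. Cost, the first endpoint in the hierarchical testing after the primary, has the same exposure if it is accumulated over follow-up periods of unequal length.

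**Working it through.** **1. The time origins side by side**

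| Place in the protocol article | Item | Origin |
|---|---|---|
| Objectives, endpoints and sample size calculation | Primary SPS at 2 years | Enrolment |
| Same section | SPS at 6, 12, 18, 24 months | Not named |
| Same section | Ultrasound in watchful waiting, start and 2 years | Enrolment |
| Implementation of the study, text | Watchful-waiting contacts at 1, 6, 12, 18, 24 months | Not named |
| Implementation of the study, Table 1 | Visits 3 to 7, including the final SPS | Surgery |

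Only Table 1 names surgery. Where another entry names an origin, it is enrolment. Randomisation is at Visit 1, so I treat enrolment and randomisation as the same date.

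**2. Consequence of applying Table 1 as written**

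Let W be the time from randomisation to surgery, which the article does not give.

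- Repair arm, operated: primary reading at W + 24 months after randomisation.
- Watchful waiting, counted from enrolment: 24 months.
- Difference between arms: W.

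The endpoint definition requires this difference to be 0.

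**3. Calendar check**

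- End of October 2014 to 1 November 2016: about 24.0 months.
- End of October 2014 to 30 November 2016: about 25.0 months.
- Enrolment origin: 24 months are needed and 24.0 to 25.0 are available, so it fits.
- Surgery origin: W + 24 ≤ 25.0 gives W ≤ about 1 month for the last recruits. Earlier recruits have correspondingly more room.

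**4. The plan's own sample size, and whether it moves**

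Inputs: SD 12.0 in both arms, expected difference 0.5 in favour of surgery, one-sided 0.05, power 80%, 286 per arm. The sample size paragraph states no margin, so it is back-solved:

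12 × √(2/286) × (1.645 + 0.842) + 0.5 = 2.495 + 0.5 = 2.995, or about 3.0.

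With a margin of 3.0, the normal approximation gives 285 per arm, and the t-test at 286 per arm has 80.05% power. Drop-out: 572 / (1 − 0.10) = 635.6, rounded up to 636. The plan's figures reproduce. None of them depends on the visit origin, so no corrected sample size follows.

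**5. Sensitivity (illustration only)**

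Assume that the timing difference moves the mean difference by a further s in favour of surgery. Power at 286 per arm is then that of a one-sided t-test with effect 3.0 − 0.5 − s and standard error 12 × √(2/286) = 1.003.

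| s (assumed) | Power |
|---|---|
| 0 | 80% |
| 0.25 | 72% |
| 0.5 | 64% |
| 1.0 | 44% |

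The values of s are assumptions and the margin is implied. The table shows how sensitive the design would be, not what will happen.

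**The case against.** The strongest reply is that this is a labelling slip. The endpoint definition and the ultrasound timing use enrolment, the abstract gives two years of follow-up to both arms, and the calendar fits enrolment. A single perioperative schedule may simply have supplied the column headings, and visit windows or a separate watchful-waiting schedule may sit in the full protocol. Much of this stands: the intended origin is very probably enrolment. But the contradiction is in the article's own text, on the primary reading, and Table 1 is presented as covering study visits generally. An unseen document does not reconcile two statements that are both printed here.

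Several stronger readings are tempting but not supported:

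- *The watchful-waiting arm has no timing at all.* It has contacts at 1, 6, 12, 18 and 24 months, and the endpoint definition and ultrasound timing point to enrolment. Only Table 1 lacks an origin usable for that arm.
- *Unoperated patients have no defined primary reading.* The endpoint definition covers pain from the hernia as well as from its repair, at two years after enrolment.
- *A watchful-waiting patient operated on late restarts the schedule.* Nothing says so.
- *Events and costs between randomisation and surgery are lost in the repair arm.* A mark at Visit 2 shows when data are collected, not when the reporting period begins. Serious adverse events, including acute incarceration, are reported to the principal investigator within 3 days, and inpatient costs are to be included in full. What remains is that the accrual period is not stated to be equal in the two arms.
- *The timing difference could produce a false claim of non-inferiority.* If postoperative pain falls with time, a later reading lowers the repair-arm score, which works against watchful waiting. The main cost would be power. The remark about falling pain supports the need for long follow-up and gives no rate of change near two years.

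**Conclusion.** Wrong as written: an internal contradiction on the timing of the primary endpoint. Table 1 counts the 24-month SPS and all other follow-up visits from surgery, while the endpoint definition counts from enrolment. Table 1 also offers no origin usable for watchful-waiting or never-operated patients.

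The size of the timing difference is the wait for surgery, which the article does not state. The planned study end tolerates about one month of it for the last recruits. The effect on the SPS contrast cannot be derived. The likely direction, favouring surgery at the expense of power, rests on the assumption that pain is still falling at two years. The sample size of 286 per arm and 636 allocated is not affected. The conclusion itself needs no numerical assumption, because it rests on the two conflicting origins.

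**What to change.** - Relabel Visits 3 to 7 in Table 1 as months after randomisation (enrolment), in both arms.
- Take the primary SPS at 24 months after randomisation, with one common visit window, regardless of whether or when surgery occurs.
- State that adverse events, serious adverse events and costs accrue from randomisation over the same period in both arms.
- Keep perioperative complication recording tied to the date of any repair, in either arm.

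The cost is a change to the Table 1 headings and the eCRF visit-window wording, plus a short note to sites. No additional patients or procedures are needed, and the planned study end already fits this origin.

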### Monitoring and statistical analysis

The Coordinating Center for Clinical Studies (KKS Charité) deals with project management, monitoring, and data management including randomization. After assessing the trial sites for qualification during a pre-study visit, the monitor will visit them on a regular basis. Visits will take place at least as follows: prior to enrolment of the first patient, three times during the course of the study, and at the time of study completion. Monitors work according to the Standard Operating Procedures (SOPs) of the KKS.

The following adverse events (AEs) are monitored (underlined): A wound infection is defined as a purulent discharge from the wound or detection of bacteria in wound samples taken using aseptic technique [27]. An intra-abdominal abscess must meet a least one of the following criteria: purulent drainage from a drain which is placed into the abdomen; organisms isolated from intra-abdominal aseptically obtained culture; abscess verified by direct examination during operation or by radiologic examination [27]. A mesh infection is defined as a detection of bacteria on the mesh with local signs of infection (redness, hyperthermia, swelling and pain) or general signs of infection like fever or tachycardia without any other reason [28]. Sepsis is recognized clinically as the presence of two or more of the following: 1) temperature greater than 38.5°C or less than 35.0°C; 2) heart rate greater than 90 bpm; 3) Respiratory rate greater than 20 bpm or PaCO2 < 32 mmHg; 4) WBC count greater than 12,000 cells/mm^3 ^or less than 4000 cells/mm^3 ^and an association with infection confirmed by culture or strongly suspected [29]. Intestinal injury or organ injury is defined as the transmural injury or the intestinal/organ wall. An enterocutaneous fistula is defined as a direct connection from the intestines to the skin with discharge of stools through the fistula.

Postoperative bleeding is defined as a bleeding requiring either blood transfusion or reoperation. Pneumonia is defined as an infection of the lung that can be caused by nearly any class of organism (bacteria, amoebae, viruses, fungi, and parasites) known to cause human infections. A urinary tract infection is an infection of one or more structures in the urinary system. A deep vein thrombosis is a blood clot in a major vein that usually develops in the legs or pelvis. Pulmonary embolism is an obstruction of a blood vessel in the lungs, usually due to a blood clot. A bowel obstruction is defined as the necessity to insert a nasogastric tube longer than 72 h after the operation or the necessity to reoperate. A recurrent hernia is a hernia diagnosed by physical examination or ultrasound after surgical hernia repair.

Other AEs are: vomiting and pain at rest. The following severe adverse events (SAEs) are monitored: reoperation, rehospitalization, ICU admission, acute incarceration, death. The principal investigator is informed about SAEs within 3 days.

An independent Data Safety Monitoring Board (DSMB) consisting of 3 external experts (2 clinical experts and 1 statistician) will meet annually to address patient safety and perform risk-benefit assessments. In accordance with its standard operating procedures (SOPs), the DSMB reviews the accumulating data from the ongoing trial to ensure continued patient safety. The DSMB assesses study aspects such as progress, integrity, and design and makes recommendations to the coordinating investigator regarding modification, continuation or termination of the study.

The primary statistical analyses will be conducted by the Institute of Biometry and Epidemiology at the Charité using an intention-to-treat (ITT) approach. Interim analysis is not planned. Additional as-treated analyses will be performed. Investigators are masked to the patient's treatment arm at the time of enrolment. The statistician will be blinded while performing data analyses.

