Thus, if both groups have a sample size of 286, a two-group 0.05 level one-sided t-test will have 80% power to reject the null hypothesis that watchful waiting is not equivalent to surgical repair in favor of the alternative that watchful waiting is not inferior to surgical intervention [18]. This leads to a total sample size of n = 2 × 286 = 572. Assuming a drop-out rate of about 10%, 636 patients will have to be allocated. Sample size calculation was done with nQuery 6.0.

The most important secondary endpoint (S1) is the cost of treatment. Hospitalization costs can be calculated yearly along the guidelines of the InEK (Institute for Hospital Reimbursement System) institute. Hospitalization costs in Germany are mapped by the German-Diagnosis Related Groups-System. Inpatient costs for each participant (operation; medical staff and nursing staff on ICU, on IMC and on general ward; medication; implants; bandaging and other material; catering; infrastructure; laboratory, radiological, endoscopic and cardiologic diagnostics) will be completely included. Hence, the exact costs of every patient can be calculated in Euro [19]. Indirect costs (time off from work) will be monitored by questionnaire during follow-up.

If the results show a statistical difference in the primary endpoint, S1 will also be tested for significance (hierarchical testing). We hypothesize lower costs in the watchful waiting group, and, if a statistical difference is found, patient satisfaction with care will be tested as another secondary endpoint S2. We also hypothesize superiority of the experimental intervention in the secondary endpoint S2 because surgery is avoided.

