Additional secondary outcomes include pain at rest, pain during exercise, highest level of pain measured by the SPS [17]. The impairment of daily activities due to pain is measured by the German version of the Pain Disability Index (PDI). The German version of the PDI revealed objectivity, reliability (Cronbach's α 0.90) and factor and construct validity [20]. Principal axis factor analysis has been used to investigate the underlying dimensions of the PDI; parallel analysis and scree plot favored a single-factor solution [21]. The functional status and quality of life is measured by the 2^nd ^German version of the SF-36 questionnaire. The reliability of the German version of the SF-36 is satisfactory, the validity is adequate, and the correlation with another established quality of life questionnaire (Nottingham-Health-Profile) is high [22]. Depression/anxiety is assessed by the 3^rd ^German version of the Hospital Anxiety and Depression Scale (HADS-D). Sensitivity and specificity were both 0.80. Reliability is high (Cronbach's α 0.80) [23]. Postoperative complications (e.g., postoperative bleeding, hematoma/seroma, wound infection, mesh infection, intra-abdominal abscess, ileus, bowel obstruction, enterocutaneous fistula, bowel injury) and mortality are recorded.

The relative frequency of acute hernia incarceration (acute incarceration events/duration of hernia) is determined in the experimental group according to the Fitzgibbons' trial in inguinal hernia [24]. To document the natural course of the hernia and a potential enlargement, hernia size is measured by ultrasound in the watchful waiting group at enrolment and after a 2-year follow-up. Therefore, ultrasound of the abdominal wall is performed and the maximum diameter of the hernia is also determined. The recurrence rate is calculated in the control group.

A flow chart of the estimated number of screened patients and the number of randomized and analyzed patients according to the CONSORT 2010 statement for reporting parallel group randomized trials [25] is given in Figure 1.

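### As printed, the bowel-obstruction definition accepts reoperation for any cause, so reoperations unrelated to obstruction can be coded as bowel obstruction (minor)

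*Protocol article*

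**What the plan says.** All places are in the protocol article.

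- **Bowel obstruction** (Monitoring and statistical analysis) is defined as "the necessity to insert a nasogastric tube longer than 72 h after the operation or the necessity to reoperate". Two alternatives are joined by *or*. Neither asks for evidence of obstruction, and the second states no reason for the reoperation.
- **Postoperative bleeding** (same section): "Postoperative bleeding is defined as a bleeding requiring either blood transfusion or reoperation". Here the condition comes first, and transfusion or reoperation sets its severity.
- **Reoperation as an event in its own right** (same section): "The following severe adverse events (SAEs) are monitored: reoperation, rehospitalization, ICU admission, acute incarceration, death". No cause is specified, which suits a general SAE category.
- **Complications recorded as secondary outcomes** (Objectives, endpoints and sample size calculation): the list includes "ileus, bowel obstruction, enterocutaneous fistula, bowel injury". Ileus and bowel obstruction are thus separate entries. The article defines the second but not the first.

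**The concern.** An adverse-event definition is there so that all sites code the same event in the same way; Trial status lists 19 sites. This one can be followed in two ways. A site that applies the words as printed codes any reoperation as a bowel obstruction. A site that applies the probable intent codes only reoperations for obstruction. The reported rate would then mix two rules.

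A reoperated bleed would also carry two labels, bleeding and obstruction, and the article does not say how such an event is counted.

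What is at stake is one line of the complication table. Both alternatives presuppose an operation, so any mislabelling falls on operated patients: mainly the repair arm, plus watchful-waiting patients who later have surgery. Complications of repair are part of the case for watchful waiting made in the Background, so a line that may hold unrelated reoperations should not be left open to misreading.

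**Working it through.** The point is one of wording, and the plan states no figure for it. The check is a literal reading, followed by a labelled illustration.

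**1. Apply the printed rule to typical reoperations.**

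- Reoperation for bleeding: meets the bleeding definition, the reoperation SAE and the bowel-obstruction definition.
- Reoperation for mesh infection, abscess, bowel injury or recurrence: meets its own definition, the reoperation SAE and the bowel-obstruction definition.
- Reoperation for obstruction: meets the reoperation SAE and the bowel-obstruction definition, as intended.

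On this reading every reoperation SAE is also a bowel obstruction. No other sentence in the article narrows the rule.

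**2. Compare the neighbouring definitions.** Bleeding starts from a bleed. Mesh infection starts from bacteria on the mesh. Abscess needs drainage, culture, operative or radiological evidence. Bowel obstruction is described only by what was done to the patient.

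**3. Look at the tube alternative.** It asks for no obstruction either, so a prolonged ileus treated with a tube could meet it, although ileus is listed separately. This is an inference from the wording. The phrase can also mean a tube kept for more than 72 hours or a tube needed later than 72 hours after surgery. On the first meaning, an obstruction managed with a shorter period of tube drainage would be missed.

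**4. What does not move.** A patient mislabelled through the reoperation alternative has, by definition, had a reoperation, which is already a monitored SAE. The number of patients with at least one AE or SAE is therefore the same with or without the extra label. The primary endpoint is pain, and S1 and S2 are cost and satisfaction; none of them uses the obstruction label.

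**5. Illustration, on assumed rates.** Denominator from the sample size section: 2 × 286 = 572; 572 / 0.90 = 635.6, rounded up to the stated 636; equal arms give 636 / 2 = 318. The article gives no rate of reoperation for causes other than obstruction. Call it r. Extra labels = 318 × r:

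- r = 1%: 3.2
- r = 2%: 6.4
- r = 3.5%: 11.1
- r = 5%: 15.9

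These are ceilings for each r. They take all 318 patients as operated and every unrelated reoperation as coded by the literal rule.

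**The case against.** The strongest reply is that the sentence is elliptical rather than wrong. It opens with bowel obstruction as its subject and sits in a list of complications, so a surgeon would read it as a threshold: an obstruction serious enough to need prolonged tube drainage or reoperation. Few would record an obstruction after reoperating for a bleed that has its own entry nearby. The article also condenses a protocol that all centres hold, and the eCRFs are complete, so the fuller text may be clear.

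Much of this stands. The intent was probably reoperation because of obstruction, and miscoding arises only where a site follows the letter. The absence of an ileus definition is also not a fault here, since an article commonly leaves that to the full protocol. But the obstruction definition itself is printed, and as printed it is too broad. Condensation explains an omission; it does not correct a stated rule.

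Three stronger readings are tempting, and the document does not support them:

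- *That obstruction will be over-counted several-fold.* The ratio is (t + r) / t, where t is the true obstruction rate. With t = 2% and r = 1% it is 1.5; with t = 0.5% and r = 3.5% it is 8. All four rates are assumptions, and the two ratios come from pairing opposite extremes. The 3.5% in the Background is a major-complication rate from another study, not a reoperation rate.
- *That the net error must be an over-count.* The reoperation alternative can only add cases, but the tube alternative may also miss some.
- *That the overall harm comparison is tilted against repair.* Reoperations are reported separately as SAEs, so the DSMB sees them whatever the label. The article states no summed event score that double labels would inflate, and the conclusion drawn in the Discussion turns on pain and incarceration.

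**Conclusion.** The point holds in a narrow form and is minor. The printed definition admits reoperation for any cause, overlaps with the bleeding definition, and duplicates the reoperation SAE. If sites code by the letter, the obstruction rate in operated patients will be misstated. The size cannot be derived from the document; the 3 to 16 extra labels depend entirely on the assumed 1% to 5% and on literal coding throughout. The finding also rests on the article alone: a clearer definition in the full protocol or eCRF would settle it. The sample size and type I error are untouched, as are the outcomes listed in step 4 of the check.

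**What to change.** Reword the definition so that the condition comes first, in the pattern already used for bleeding: a bowel obstruction that meets the existing 72-hour tube criterion, or that requires reoperation because of the obstruction. State which meaning of the 72-hour phrase applies, and reconcile the tube criterion with the separate ileus entry so that sites know where a prolonged ileus belongs. Add a field to the eCRF for the cause of each reoperation.

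Nothing wider is needed. Mandatory imaging confirmation or forcing each event to a single cause would go beyond the defect, and single-cause attribution could hide complications that truly coexist.

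The cost is a sentence or two and one eCRF field, with no added visits or patients. The downside is small: the eCRFs are already built and the first patient has been randomized, so the form must be amended and any events already coded need checking.

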## Abbreviations

AE: Adverse Event; ASA: American Society of Anesthesiologists; AWARE: Watchful Waiting vs. Repair of Oligosymptomatic Incisional Hernias; BMBF: Bundesministerium für Bildung und Forschung (Federal Ministry of Education and Research); bpm: Beats per minute; CI: Confidence interval; CONSORT: Consolidated Standards of Reporting Trials; DFG: Deutsche Forschungsgemeinschaft (German Research Foundation); DSMB: Data Safety Monitoring Board; eCRF: Electronic Case Report Form; HADS-D: Hospital Anxiety and Depression Scale - Deutsche Version (German version); ICU: Intensive Care Unit; IMC: Intermediate Care Unit; InEK: Institut für das Entgeltsystem im Krankenhaus (Institute for Hospital Reimbursement System); IPOM: Intraperitoneal onlay mesh; ITT: Intention-to-treat; KKS: Koordinierungszentrum für Klinische Studien (Coordinating Center for Clinical Studies); OP: Operation; PDI: Pain Disability Index; SAE: Serious Adverse Event; SD: Standard deviation; SF-36: Short Form 36 Health Survey Questionnaire; SOP: Standard operating procedure; SPS: Surgical Pain Scales.

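### The printed SAE list is closed and has no outcome-based criteria, so some serious index-stay complications fall outside the 3-day notice

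*Protocol article*

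**What the plan says.** The AE definitions in the Protocol article, Monitoring and statistical analysis, open with "The following adverse events (AEs) are monitored (underlined". They cover wound, mesh and intra-abdominal infection, sepsis, organ injury, fistula, bleeding, pneumonia, thrombosis, embolism, bowel obstruction and recurrence. The SAE definition follows separately: "The following severe adverse events (SAEs) are monitored: reoperation, rehospitalization, ICU admission, acute incarceration, death". The next sentence gives the only expedited route in the article: "The principal investigator is informed about SAEs within 3 days".

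The same abbreviation is expanded differently under Abbreviations: "SAE: Serious Adverse Event".

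Safety information is also collected in other ways:
- Objectives, endpoints and sample size calculation records postoperative complications and mortality as secondary outcomes.
- Table 1 collects AEs and SAEs at every visit from the day of surgery to 24 months, and postoperative complications at 1, 12 and 24 months.
- The DSMB meets annually and reviews the accumulating data.

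**The concern.** Four of the five SAE items are consequences of an event (a further operation, a further admission, an ICU stay, death). Only one, acute incarceration, is a diagnosis. A patient who has a serious complication while still in hospital for the repair cannot be rehospitalized for it. If it is handled on the ward or within the same operation, no item on the list applies.

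This matters for safety oversight. The 3-day notice is the only fast route that the article states, and these events fall outside it and outside any SAE tabulation. The characteristic harm of watchful waiting is always inside. The wording is also loose in other places: ICU admission is unqualified, rehospitalization presupposes an earlier stay, and *severe* grades intensity whereas *serious* refers to outcome.

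**Working it through.** The plan gives no figure on this point, so there is none to reproduce. The check sets the AE definitions beside the five SAE items, for an event in the index stay.

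| Event, as defined in the article | SAE item that applies without reoperation, ICU admission or death |
|---|---|
| Sepsis: "Sepsis is recognized clinically as the presence of two or more of the following" (temperature, heart rate, respiratory and white-cell criteria, with infection) | None |
| Organ injury: "Intestinal injury or organ injury is defined as the transmural injury or the intestinal/organ wall", repaired in the same operation | None |
| Fistula: "An enterocutaneous fistula is defined as a direct connection from the intestines to the skin with discharge of stools through the fistula" | None |
| Pulmonary embolism | None |
| Bleeding: "Postoperative bleeding is defined as a bleeding requiring either blood transfusion or reoperation" | None for the transfusion branch; the reoperation branch is an SAE |
| Bowel obstruction: nasogastric tube beyond 72 h, or reoperation | None for the tube branch; the reoperation branch is an SAE |
| Acute incarceration | Always an SAE, by name |

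The bleeding and obstruction rows show the gap most plainly. One defined event splits into an SAE and a non-SAE solely by whether the patient returned to theatre.

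**Is the list really closed?** It carries no marker of examples and no residual item. The article does use such a marker when it lists postoperative complications among the secondary outcomes, so the authors distinguish the two forms.

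**Wording in the other direction.** Inclusion and exclusion criteria excludes only ASA scores above 3, so ASA 3 patients can enter. The cost paragraph counts ICU care among inpatient costs. A planned postoperative ICU night is therefore plausible and, as worded, is an SAE. The article does not say how often this would happen.

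**Admissions.** Read literally, rehospitalization needs a previous hospitalization. A watchful-waiting patient's first admission may or may not count; the text does not settle it.

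**Size, for context only.** Inputs: 636 patients to be allocated, equally (the calculation uses 2 × 286), so 636 / 2 = 318 per arm. Background gives 3.5% major complications, 10.7% overall morbidity and 11.2% rehospitalization from a cited Danish study. Assuming that those rates carry over to this trial:
- major complications: 318 × 0.035 = 11.1, about 11;
- any morbidity: 318 × 0.107 = 34.0, about 34;
- rehospitalization: 318 × 0.112 = 35.6, about 36, all SAEs under the printed list.

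The article does not say what share of major complications is managed in the index stay without reoperation, ICU admission or death, nor how the cited study defined major. If serious is taken to mean major in that sense, the number outside the list lies anywhere from 0 to about 11.

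**The case against.** **The events are not lost.** They are monitored AEs, the main surgical ones are named again as secondary outcomes, collection runs from surgery to 24 months, and DSMB review is not limited to SAEs. This stands. What remains is the lack of a stated expedited notice; the other stated routes are scheduled visits and an annual meeting.

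**No SAE comparison is planned.** A reader might infer that the list biases a between-arm SAE comparison and under-counts surgical harm. The document does not support that: it states no such comparison. The errors also run in both directions, because planned ICU stays would add SAEs in the repair arm, while the count of first admissions under watchful waiting is unclear. A net under-count is not shown.

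**The size cannot be given.** Assuming some share of the 11 major complications and reporting it as a percentage under-count would only return the assumption. It would also ignore the roughly 36 rehospitalizations that do count. This stands in full.

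**The route for ordinary AEs is unknown.** One might say that these events reach the principal investigator only as ordinary AEs, but the article does not describe how AEs reach that person.

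**This is a condensed article.** Seriousness criteria may sit in the full protocol, which the centres hold and which is not shown. This limits the point to the printed list. It does not remove it: the article sets out AE definitions at length, states a definite SAE list and ties the notice to it. Followed as written, that rule works badly.

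**Conclusion.** The point holds for the printed rule. The SAE list is closed and has no item for prolongation of a stay, a life-threatening event or lasting disability. Serious index-stay complications without reoperation, ICU admission or death are therefore outside the stated 3-day notice and any SAE tabulation, while acute incarceration is always inside. Those that do lead to reoperation, ICU admission or death are covered, as are readmissions after first discharge. The treatment of planned ICU stays and of first admissions under watchful waiting also needs settling, and *severe* must be reconciled with *serious*.

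Neither the size nor the net direction of a miscount can be derived; the range of 0 to about 11 rests on the background rate applying here. The point is about safety reporting and does not touch the primary endpoint or the sample size. It assumes that the full protocol contains no general seriousness criteria that override the printed list.

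**What to change.** In Monitoring and statistical analysis, define an SAE by outcome and identically in both arms: death, a life-threatening event, unplanned admission or prolongation of a stay, or lasting disability. Keep acute incarceration and the other listed triggers. State that pre-planned ICU observation after surgery is not an SAE. Use *serious* throughout, as under Abbreviations. If the full protocol already holds such criteria, align the printed list with them.

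There is no need to declare further diagnoses always serious. Under the printed sepsis definition, a heart rate above 90 with a white-cell count above 12,000 and strongly suspected infection would qualify, so outcome criteria separate cases better than a longer list of names.

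The cost is protocol and eCRF wording and a few more SAE forms, mostly in the repair arm. Trial status reports the eCRFs as complete and the first patient as randomized, so the change would come as an amendment.
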